### Accrual rate

The anticipated accrual rate is 75 patients in 2 years.

### Progression free survival

Analysis of the secondary endpoint of improved progression free survival will take into account patient stage subgroups. However, as the numbers in this study are small, a meaningful subgroup analysis may not be possible.

### Participant follow-up

Participation in this study is voluntary; patients will be able to withdraw at any time. Patients will be asked to present for clinical follow-up four monthly for the two years following treatment of their primary melanoma. Those who withdraw from treatment will be asked to continue follow-up visits according to the protocol even though they have stopped treatment, to allow collection of outcome data. If a patient decides to stop their follow-up visits, their health status will be periodically ascertained by way of phone contact with their general practitioner or by direct phone contact. The National Death Index at the Australian Institute of Health and Welfare will be used to collect survival information on patients who have been lost to follow-up.

After completion of active follow-up, recurrences will be ascertained through the New South Wales Central Cancer Registry and deaths through the National Death Index for a period of five years after date of diagnosis.

### Blinding

Patients and physicians are blinded to both study treatment allocation and vitamin D levels.

### Statistical methods

Analysis of primary endpointsThe percentage of patients achieving a serum 25OHD above 80 nmol/l at 12 and 24 months receiving treatment will be reported. Summary statistics of serum 25OHD concentrations will be reported for both groups at 12 and 24 months.Dose adherence will be reported as the percentage of dose taken compared to the prescribed monthly dose as calculated from the patient diary and study forms. A 95% confidence interval will be reported to check if the expected rate of 80% dosage of study tablets for the duration of the study protocol by all patients is obtained.Safety outcomes will be reported as the proportions of patients exceeding the following maxima, as well as summary statistics where appropriate.Analysis of secondary endpointsParticipation rate will be reported as the proportion of subjects eligible and invited to participate who agree to be randomised. A 95% confidence interval will be reported to check if the expected rate of 60% was obtained.Progression free survival will be displayed using Kaplan-Meier survival curves.

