#### Secondary endpoints

The secondary endpoints will be met if the following criteria are achieved:If 60% of eligible patients agree to participate and the study accrues 75 patients in 2 yearsImproved progression free survival

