### Sample size and randomisation

The design of the study is an optimal two-stage phase II trial using the approach of Simon [41]. Sample sizes are determined separately for the two cohorts. The two cohorts, those receiving vitamin D and those receiving placebo, will be analysed separately. Assuming a lower limit of efficacy of 48% and a regimen activity level of 68%, the study would proceed in two stages. In the first stage, if more than 7 patients with serum 25OHD less than 80 nmol/l are observed in the first 14 patients in the active arm, consideration will be given to either modifying the regimen or stopping the study due to inactivity.

Twenty-five patients (in a 2:1 randomisation) will be accrued to the placebo arm to allow adequate data to estimate concentration of serum 25OHD in an untreated cohort. Thus it is proposed to accrue a total of 75 patients into the study, 50 receiving vitamin D and 25 receiving placebo. These calculations are based on power of 80% with 95% confidence and allow for a modest dropout rate.

Patients will be centrally randomised by the Australian National Health and Medical Research Council (NHMRC) Clinical Trials Centre using a computerised interactive voice response system (IVRS). Patients will be stratified by gender.

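### Improved progression-free survival is set as a met-or-not-met criterion, but no stated statistic can decide it and the trial is not sized for it

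*Protocol article*

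**What the plan says.** All references are to the protocol article.

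- **Secondary endpoints.** The list opens with "The secondary endpoints will be met if the following criteria are achieved". It has two entries: participation and accrual (60% of eligible patients agreeing, 75 patients in 2 years), and improved PFS. The first has numbers attached. The second has none.
- **Statistical methods, secondary endpoints.** For participation: "A 95% confidence interval will be reported to check if the expected rate of 60% was obtained". For PFS: "Progression free survival will be displayed using Kaplan-Meier survival curves".
- **Progression free survival.** "Analysis of the secondary endpoint of improved progression free survival will take into account patient stage subgroups", followed by the reservation that "as the numbers in this study are small, a meaningful subgroup analysis may not be possible".
- **Sample size and randomisation.** The plan is to accrue "a total of 75 patients into the study, 50 receiving vitamin D and 25 receiving placebo", with randomisation stratified by gender. The size is justified by a Simon two-stage design on serum 25OHD.

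**The concern.** The wording "improved progression free survival" is comparative. It needs a contrast between vitamin D and placebo and a rule for when that contrast counts as improvement. The analysis stated for PFS is a display, which supplies neither. The one addition, stage subgroups, has no method and is hedged in the next sentence. Stage is also not a randomisation stratum, so the design does not balance it between 50 and 25 patients.

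The stake is how the result is described. The abstract says favourable outcomes will form the basis for a phase III trial on time to recurrence and survival. If PFS is reported as met or not met, either label would claim more than so few events can support. An estimate with its interval would show how little is known.

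**Working it through.** **1. Criterion against analysis.** The secondary criteria and the adherence criterion, set against what the article states for judging them:

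| Criterion | Stated target | Stated means of judging |
|---|---|---|
| Dose adherence (primary) | more than 80% of dose | 95% interval compared with 80% |
| Participation (secondary) | 60% of eligible patients | 95% interval compared with 60% |
| PFS (secondary) | improved | Kaplan-Meier display; stage subgroups, method not named |

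PFS is the only row in which the stated means cannot return an answer to the stated criterion.

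**2. What the trial was sized for.** The article gives no event count, hazard ratio or power for PFS. Its own figure is the active-arm size from the Simon optimal design with 48% versus 68%, 80% power and 95% confidence (taken as one-sided alpha 0.05). An exact binomial search gives a first stage of 14 and a total of 46, with alpha 0.044 and power 0.805. The first stage of 14 matches the article. With an assumed 8% dropout (the article says only that it is modest), 46 / (1 − 0.08) = 50, which is the stated active arm. The sizing reproduces, and PFS plays no part in it.

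**3. Information on PFS.** With allocation 2/3 to 1/3 and *d* events, the standard approximation is

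SE(log HR) = 1 / √(*d* × 2/3 × 1/3) = 1 / √(2*d*/9).

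The 95% interval is the estimate multiplied and divided by exp(1.96 × SE). Two-sided 5% power is Φ(|ln HR| / SE − 1.96).

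For *d* = 20 (assumed): SE = 1 / √4.444 = 0.474, and the interval factor is exp(1.96 × 0.474) = 2.53.
- HR 0.5: 0.693 / 0.474 − 1.96 = −0.50, so power is 31%.
- HR 0.7: 0.357 / 0.474 − 1.96 = −1.21, so power is 11%.

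The final event count is not in the article, so a range is needed:

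| Events | Share of 75 | 95% interval factor | Power, HR 0.5 | Power, HR 0.7 |
|---|---|---|---|---|
| 10 | 13% | 3.72 | 18% | 8% |
| 20 | 27% | 2.53 | 31% | 11% |
| 37 | 49% | 1.98 | 51% | 17% |

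Ten is the number of recurrences given under Feasibility. It is an interim count, pooled over arms, when 21 patients had completed 24 months. Twenty and 37 are assumptions.

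**4. What would be needed.** For 80% power, *d* = (1.96 + 0.842)² / [(2/9) × (ln HR)²]. This gives 74 events for HR 0.5 and 278 for HR 0.7, in a trial of 75 patients. A formal test would therefore not rescue the criterion.

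**The case against.** The article condenses a longer protocol, and a statistical analysis plan may exist. A log-rank test, a hazard ratio or covariates for a secondary survival endpoint are commonly left to those documents, so it cannot be said that no estimate is planned. PFS is not among the trial objectives, the abstract lists it without the directional word, and the small numbers are conceded. All of this stands, and it limits the weight of the point. It does not remove the success wording, which would be unsuitable for a trial of this size whatever an unseen plan adds.

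A reader might infer four stronger claims. The article does not support them.

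- *PFS will be judged by eye and would look favourable about half the time under no effect.* Simulation of 50 versus 25 patients with no effect does give log-rank observed minus expected events favouring vitamin D in 48.9% to 49.6% of trials, for assumed 24-month PFS of 87% to 50%. But the article states no visual rule, and a figure near one half holds for any directional reading of two equal arms.
- *The arms will never be compared.* The sentence "The two cohorts, those receiving vitamin D and those receiving placebo, will be analysed separately" stands among the sample-size statements for the 25OHD design. It cannot bar every comparison, because a primary kidney-function criterion compares eGFR between the arms.
- *Kaplan-Meier curves are the whole analysis and stage will go unadjusted.* The Progression free survival section says stage will be taken into account and leaves the method open.
- *The factor of 3.7 at 10 events describes the final analysis.* Follow-up was incomplete, and the Participant follow-up section provides for ascertaining recurrences and deaths up to five years after diagnosis.

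**Conclusion.** The point holds as an inconsistency on the page: a met-or-not-met criterion of improvement is paired with a display and hedged subgroups, and nothing stated can decide it. The mismatch itself rests on no assumption. Its size does. At an assumed 20 events, the hazard ratio would be known only to within a factor of about 2.5, with about 31% power for a halving of the hazard. Over 10 to 37 events the factor runs from 3.7 to 2.0 and that power from 18% to 51%. These figures use the simple large-sample formula under 2:1 allocation and ignore the small further loss from stratifying by stage. Severity is minor, because this is a secondary endpoint of a pilot, and no passage makes phase III depend on PFS specifically.

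**What to change.** 1. **Secondary endpoints:** remove improved PFS from the criteria to be met. List PFS as a descriptive endpoint with no success rule.
2. **Statistical methods:** beside the Kaplan-Meier curves, report the vitamin D versus placebo hazard ratio with its 95% confidence interval, labelled descriptive. Take it from a Cox model stratified by stage (II versus III). Add sex, the randomisation stratum, only if the event count allows. Under no effect, one third of events fall on placebo, which is about 3 of 10 or 7 of 20, so a model with both factors may be unstable.
3. **Progression free survival:** let the stratified model replace reliance on stage subgroups, and drop the directional word.

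The cost is a few sentences and one model, on data already scheduled: tumour status at each four-monthly visit, with stage and sex known at entry. The sponsor can no longer declare a PFS endpoint met, and the wide interval will be visible.

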### Quality assurance

An independent Data Safety Monitoring Committee will periodically review the study for efficacy and safety. Efficacy will be reviewed after the first 14 patients in the active arm have completed 4 and 12 months of the vitamin D regimen. Safety data will be reviewed after 20 patients have completed 4 and 12 months of treatment and again when 35 patients have completed 12 months of treatment.

## Discussion

### Feasibility

Initial accrual to the ANZMTG 02.09 Mel-D study was slow, however a number of strategies have recently worked well in the early identification of eligible patients. All histopathology reports from wide excisions of melanoma are checked by the clinical trials staff and potentially eligible study participants are identified. The melanoma surgeons are reminded about study eligibility criteria prior to that patient’s consultation. In addition, a one-page Mel-D trial synopsis detailing the inclusion and exclusion criteria has been placed in the surgical consulting rooms and frequent updates of the trial progress are reported at the MIA research meetings. The study is promoted regularly on the ANZMTG website, membership newsletter and at various meetings (including the Annual Scientific Research Meeting).

Approximately 50% of eligible patients have participated in the study. The target accrual of 75 patients has been achieved and 21 patients have completed the full 24 months of treatment and follow-up. However, 10 patients have developed recurrence and ceased the trial. Planning for a phase III trial is underway, to open to melanoma treatment sites outside the Melanoma Institute Australia.

### Registration

This trial is registered with the Australia and New Zealand Clinical Trials Registry (ANZCTR) #ACTRN12609000351213.

#### Comprehensive inclusion and exclusion criteria for ANZMTG 02.09 Mel-D study

##### Inclusion criteria

18–79 years of agePrimary, histologically confirmed resected stage IIb, IIc, IIIa (N1a, N2a) and IIIb (N1a, N2a) cutaneous melanomaWide excision or, if there is no wide excision, excision of the primary lesion with clear pathological margins <120 days prior to randomisation, with or without sentinel node biopsySerum corrected calcium and Serum creatinine are ≤1.5 times the institutional upper limit of normal and eGFR within normal range for testing laboratorySerum lactate dehydrogenase < 1.5 upper limit of normalWritten informed consentGeographically accessible and willing and able to attend 4 monthly follow-up at MIA for 2 yearsPerformance status ECOG 0–2 (see Appendix 1)

#### Exclusion criteria

Patients with a known history of renal calculi.Patients with a known history of hyperparathyroidism.Patients who have a concomitant invasive cancer other than basal cell carcinoma of the skin or localized squamous cell carcinoma of the skin or a previous such cancer and have been cancer free for less than 5 years.Any of the following laboratory test results (tests must not have been carried out more than four weeks prior to randomisation)Absolute neutrophil count < 1.5 × 10^9^/LPlatelet count < 100 × 10^9^/LTotal bilirubin > 1.5 upper limit of normalAST, ALT, Alk Phos > 2.5 upper limit of normalPatients who are pregnant or lactating. Women of child bearing potential must have a confirmed negative pregnancy test at study entry.Patients with a medical or psychosocial problem which, in the investigators opinion, would interfere with treatment or follow-up.Patients with either ocular or mucosal melanomaPatients who are currently enrolled in trials of other experimental treatments or alternative therapiesPatients cannot have received any other. investigational agents or treatments (i.e. chemo-, immuno-, vaccine or radiotherapy) within 30 days of commencing study.Patient should not be taking other agents known to interact with the study drug, such as anti-convulsants.

### Appendix 2

#### Safety procedures in the event of abnormal assay results

##### Dose modification

■ If serum 25OHD is >200 nmol/l 4–6 weeks after the first dose is given, discontinue all treatment and recommence monthly treatment if and when it falls to <120 nmol/l on 4 monthly monitoring.■ If serum corrected calcium, 24 hour urinary calcium excretion or urinary calcium to creatinine ratio is above the normal range by <20% of the upper limit of normal, discontinue treatment until it returns to within the normal range, then recommence monthly treatment. In the event of temporary discontinuation for either of these reasons, measure 25OHD on stored serum from blood sample collected at the time of the elevated calcium or calcium to creatinine ratio if not a routine 25OHD measurement time.

##### Dose cessation

■ eGFR, serum corrected calcium, 24 hour urinary calcium excretion, or calcium to creatinine ratio is >20% above laboratory normal range.■ Development of a renal calculus while on study treatment.■ Pregnancy occurring during the course of the trial.■ Disease progression.

##### Concomitant medications/treatments

Concomitant medications will not be recorded during the study, except for medications used to treat adverse events or medications known to interact with the study medications. ■ Anti-convulsant medication is not allowed.■ Any concomitant use of vitamin D or multi-vitamin supplements in sufficient detail to be able to estimate daily vitamin D intake from these sources.■ Any concomitant use of calcium supplements.
